## Abstract

**Background:**

It is uncertain whether awake prone positioning can prevent intubation for invasive ventilation in spontaneous breathing critically ill patients with acute hypoxemic respiratory failure. Awake prone positioning could benefit these patients for various reasons, including a reduction in direct harm to lung tissue, and prevention of tracheal intubation-related complications.

**Design and methods:**

The PRONELIFE study is an investigator-initiated, international, multicenter, randomized clinical trial in patients who may need invasive ventilation because of acute hypoxemic respiratory failure. Consecutive patients admitted to participating ICUs are randomly assigned to standard care with awake prone positioning, versus standard care without awake prone positioning. The primary endpoint is a composite of tracheal intubation and all-cause mortality in the first 14 days after enrolment. Secondary endpoints include time to tracheal intubation and effects of awake prone positioning on oxygenation parameters, dyspnea sensation, and complications. Other endpoints are the number of days free from ventilation and alive at 28 days, total duration of use of noninvasive respiratory support, total duration of invasive ventilation, length of stay in ICU and hospital, and mortality in ICU and hospital, and at 28, 60, and 90 days. We will also collect data regarding the tolerance of prone positioning.

**Discussion:**

The PRONELIFE study is among the first randomized clinical trials investigating the effect of awake prone positioning on intubation rate in ICU patients with acute hypoxemic failure from any cause. The PRONELIFE study is sufficiently sized to determine the effect of awake prone positioning on intubation for invasive ventilation—patients are eligible in case of acute hypoxemic respiratory failure without restrictions regarding etiology. The PRONELIFE study is a pragmatic trial in which blinding is impossible—however, as around 35 ICUs worldwide will participate in this study, its findings will be highly generalizable. The findings of the PRONELIFE study have the potential to change clinical management of patients who may need invasive ventilation because of acute hypoxemic respiratory failure.

**Trial registration:**

ISRCTN ISRCTN11536318. Registered on 17 September 2021. The PRONELIFE study is registered at clinicaltrials.gov with reference number NCT04142736 (October, 2019).

## Background

Acute hypoxic respiratory failure represents one of the most common reasons for intensive care unit (ICU) admission [1]. Initial management of hypoxemic patients should involve immediate administration of simple supplemental oxygen via a nasal prong or a non-rebreather mask, or more complex forms of respiratory support like high-flow nasal oxygen (HFNO) oxygen or noninvasive ventilation (NIV), depending on severity of hypoxic respiratory failure and the underlying cause, but also patient characteristics and the availability of oxygen interfaces. Unfortunately, patients with acute hypoxemic respiratory failure often need to proceed with invasive ventilation. While life-saving, this intervention comes with disadvantages, including ventilator-induced lung injury and respiratory muscle waist, but also intubation-related side-effects. In addition, intubated patients often need sedation, which has side-effects of its own.

In intubated invasively ventilated ICU patients, prone positioning can be used to improve oxygenation, and this intervention has been shown to improve outcome in patients with severe ARDS. This survival benefit could be mediated, at least in part through a reduction in direct harm to lung tissue, as regional differences in lung aeration, compliance, and shear strain are minimized by this intervention [2, 3]. In theory, nonintubated patients could also benefit from prone positioning [4, 5], a strategy named “awake prone positioning” [6, 7]. Some evidence for benefit of awake prone positioning comes from a handful of studies, mostly case reports and single-center observation case series [5, 8, 9]. The findings thus far show that awake prone positioning can indeed improve oxygenation and also reduce dyspnea sensation. Besides that, awake prone positioning seems to be well-accepted and easy to perform, and to have relatively few side-effects [10].

In the absence of sufficient randomized clinical trial evidence, we designed the PRONELIFE study, a pragmatic study that compares standard care with awake prone positioning versus standard care without awake prone positioning in patients with acute hypoxemic respiratory failure from any cause. We hypothesize that awake prone positioning reduces the need for intubation.

## Methods

### Design

The “PRone positioN in patients with spontanEous ventiLation and acute hypoxemic respIratory FailurE” (PRONELIFE) study is a pragmatic, investigator-initiated, international and multicenter, two-arm, superiority randomized clinical trial in patients with acute hypoxemic respiratory failure from any cause. The study will be conducted according to the Declaration of Helsinki principles as stated in the current version of Fortaleza, Brazil, 2013 [11]. The Institutional Review Board of the Sagrat Cor University Hospital, Barcelona, Spain, approved the study protocol (reference number 2019/68-UCI-HUSC). The study is registered at www.clinicaltrials.gov (NCT04142736, October 2019). The PRONELIFE study is planned to be performed in the 35 ICUs worldwide. Patients will be provisionally included under a strategy of deferred consent, for reasons as explained below.

### Consort diagram

The Consolidated Standards of Reporting Trials (CONSORT) [12] diagram of the PRONELIFE study is presented in Fig. 1. Consecutive patients admitted to the participating ICUs are screened for eligibility. Demographic data are registered regardless of meeting enrollment criteria. If excluded from participation, the reason(s) for exclusion will be reported. The study overview is presented in Fig. 2.

**Fig. 1 Fig1:**
[figure not shown]
Consolidated Standards of Reporting Trials (CONSORT) diagram

**Fig. 2 Fig2:**
[figure not shown]
Study overview

### Inclusion and exclusion criteria

Patients admitted to the ICU with acute hypoxemic respiratory failure from any cause will be eligible for participation, unless prompt intubation is irrepressible (Table 1). Acute respiratory failure is defined as the need for supplementary oxygen with an FiO_2_ of at least 40% by Venturi facemask, HFNO, NIV, or CPAP needed to achieve and maintain an SpO_2_ of between 88 and 92%.

**Table 1 Tab1:** Contraindication for awake prone position

• Suspected increased intracranial pressure (e.g., severe brain injury) • Hemoptysis • Vomiting • Recent abdominal wound (less than 15 days) • Tracheal surgery or sternotomy during the previous 15 days • Facial trauma or facial surgery during the previous 15 days • Deep venous thrombosis treated for less than 2 days • Cardiac pacemaker inserted in the last 2 days • Unstable spine, femur, or pelvic fractures • Hemodynamic instability (defined by a systolic blood pressure below 90 mmHg, mean blood pressure below 65 mmHg, or requirement for vasopressor) • Pregnant women • Presence of chest tube	

The PRONELIFE study has the following exclusion criteria: age < 18 years, having any contraindication for prone positioning (Table 2), previous participation in this trial, and participation in other interventional trials with the same primary endpoint. We also exclude pregnant patients, patients who refuse intubation, and those only receiving comfort care. As patients will be provisionally included under a strategy of deferred consent, there is no need for written informed consent at start of the study—however, if consent is not obtained within 48 h, a patient drops out of the study and will be replaced.

**Table 2 Tab2:** Borg dyspnea scale

0	Nothing at all
0.5	Very, very slight (just noticeable)
1	Very slight
2	Slight breathlessness
3	Moderate
4	Somewhat severe
5	Severe breathlessness
6	
7	Very severe breathlessness
8	
9	Very, very severe (almost maximal)
10	Maximal

### Study endpoints

The primary endpoint is the composite of tracheal intubation and all-cause mortality within 14 days after enrollment.

Secondary endpoints are the effects of awake proning on the following clinical outcome variables:
Time to tracheal intubation (only in patients who need invasive ventilation);Oxygenation parameters;Dyspnea sensation (while awake in prone versus supine position);The number of days free from invasive ventilation and alive at day 28;Duration of use of noninvasive ventilatory support, including the use of a non-rebreather mask, CPAP, high-flow nasal oxygen (HFNO) oxygen, or noninvasive ventilation (NIV);Duration of invasive ventilation;Ventilation-free days (VFD) at 28 days from ICU admission, defined as the number of days alive and free from IMV during the first 28 days from start of IMV;Length of stay in ICU and hospital;Mortality in ICU and hospital, and at 28, 60, and 90 days; andTolerance of prone positioning (only in patients in the prone positioning group).

### Randomization and blinding

Randomization will be performed using a dedicated password-protected website and will be balanced per center. Central randomization with the use of a permutated-block randomization list (with block sizes of 4 to 8) will be used. Participants will be allocated to the prone positioning or standard care on a 1:1 ratio. By the nature of the intervention, it will not be possible to blind clinicians to whether a participant has been randomized to awake proning or standard care. Interventions will be blinded to data analysts and outcome assessors.

### Prone positioning

The study intervention will last for at least 48 h and is divided in 4 blocks of 6 h each: patients will be placed in the prone position for up to 2 h, which can be prolonged if the patient feels comfortable, but could also be interrupted if a patient meets any of the discontinuation criteria which are any of the following:
Developing a contraindication (Table 1);Worsening of dyspnea (at any time, according to predefined criteria, as described in Table 2);A further and sustained drop in SpO_2_ refractory to an increase in FiO_2_; nausea or vomiting; andIncreasing hemodynamic instability that is unrelated to sedatives (if given) and cannot be corrected by vasopressor or inotrope infusion (as described in Table 3)

**Table 3 Tab3:** Hemodynamic instability definition

Defined as any of the following not responding to fluid resuscitation:	
• Systolic arterial pressure < 90 mmHg, or • Mean arterial pressure < 65 mmHg, or • Increased needs of vasopressor agents, or • ECG evidence of ischemia or significant uncontrolled ventricular arrhythmia	

During the change in position, from supine to prone or from prone to supine, FiO_2_ will be increased by 25% above baseline. Each change in position is guided by two healthcare workers and an attending physician, but more healthcare workers could be needed. While the patient remains in a prone position, skin protection will be used to avoid pressure sores. Also, the application of cushions will enhance patient tolerance. Arms can be at the side, in a swimmer’s position, and can be moved to increase comfort.

Food and comfort breaks are planned while patients are in supine. If the patient is receiving enteral or oral feeding, this is interrupted from 1 h before prone until a patient is in a supine position.

The best-fitting and most-tolerated oxygen interface will be used in the prone position—this could be different from patient to patient, and different from what is used in the supine position, and could differ between patients but also institutions (i.e., depending on the availability of masks with or without a reservoir bag and with or without the Venturi system, HFNO, CPAP or NIV).

### Standard of care

In all patients, whether receiving prone positioning or not, the best standard of care is provided, according to the standard care by the local teams.

When in a supine position, the patient will be placed in 30–45° semi-recumbent position but this can be changed for the comfort of the patient to supine, semi-sitting, sitting, or a lateral decubitus position.

Vitals parameters, including SpO_2_ and the SpO_2_/FiO_2_, are continuously monitored. The oxygenation target ranges for SpO_2_ are 88 to 92%; this is 7 to 8 kPa for PaO_2_. For patients in whom the risk of potentially dangerous hypoxemia could become unacceptable during the study (e.g., in patients who develop cardiac ischemia due to cardiac infarction or failed revascularization, or severe untreatable anemia such as with Jehovah’s Witnesses), oxygenation target ranges can be higher, 94 to 96% for SpO_2_ and 9 to 11.5 kPa for PaO_2_ [13–15].

Opiates and benzodiazepines are allowed at low dosages to improve comfort.

### Intubation criteria

The decision to continue with invasive mechanical ventilation is based on clinical judgment rather than isolated gasometrical criteria. Any of the following criteria should be considered for proceeding to endotracheal intubation:
Respiratory or cardiac arrest;Respiratory pauses;Altered level of consciousness such as uncontrolled agitation not responding to medical treatment, or a drop in the Glasgow Coma Score;Evidence of exhaustion such as an unacceptable increase in use of accessory muscles or thoracoabdominal paradox;Inability to clear secretions from the airway in patients with abundant sputum production, or evidence of aspiration; orHemodynamic instability as defined in Table 3

In addition, the presence of 2 of the following criteria within 1 h of start noninvasive ventilatory support:
Respiratory rate > 35 breaths/min, or increased respiratory rate from the baseline;Not improving or increased dyspnea;pH < 7.30 or less from its baseline, or PaCO_2_ > 20% from the baseline value; orSpO_2_ < 88%

### Weaning from the noninvasive oxygen delivery system

Weaning from the oxygen therapy delivery system will be done according to local protocols and preferences. Table 4 provides guidance for oxygen requirements coupled with the reduction in gas flow rates of the HFNO.

**Table 4 Tab4:** High-flow nasal cannula scheme for oxygen requirements coupled with gas flow rates

FiO_2_	21–30%	30–40%	40–60%	60–100%
Flow	30 L/min	30–40 L/min	40–50 L/min	50–70 L/min

In case the patient is using NIV, sessions could be interrupted when the respiratory rate is < 25 breaths/min and the FiO_2_ < 40% (for a SpO_2_ 88%)

### Invasive ventilation

If patient continues with invasive ventilation, settings are chosen in line with the local guidelines for invasive ventilation. The use of lung-protective ventilation with a low tidal volume and low pressures is advocated. Also, sufficient levels of PEEP should be used, and prone positioning is to be applied if a patient develops severe hypoxemia, defined as PaO_2_/FiO_2_ < 150 mmHg at a minimum FiO_2_ of 60% and 5 cmH_2_O.

### Fluid regimens

We advise to use a restricted fluid strategy, i.e., targeting a neutral cumulative fluid balance as soon as a patient can be weaned of vasopressors. Crystalloid infusions are preferred over colloid infusions.

### Sedation

In patients under invasive ventilation, the local guideline for sedation is to be followed, and preferably consists of combinations of use of analgo-sedation over hypno-sedation, use of bolus over continuous infusion of sedating agents, and the use of sedation scores (e.g., 3 times per day, and using a Richmond Agitation Sedation Scale) [16, 17]. Also, the level of pain is to be determined, e.g., by using the Numeric Rating Scale, the Visual Analog Scale (VAS), the Critical Care Pain Observation Tool (CCPOT) or Behavioral Pain Scale (BPS).

### Weaning from invasive ventilation

Weaning from invasive ventilation follows local protocols and preferences. In all patients, it should be tested whether the patient accepts assist ventilation at least two times a day; this should also be tried when the patient shows respiratory muscle activity during assist ventilation. The attending physician decides when to extubate a patient, based on general extubation criteria (i.e., responsive and cooperative, adequate cough reflex, adequate oxygenation with FiO_2_ ≤ 0.4, hemodynamically stable, no uncontrolled arrhythmia and a rectal temperature > 36 °C, and after successfully passing a spontaneous breathing trial (SBT) with a T-piece or ventilation with minimal support (pressure support level < 10 cmH_2_O) and FiO_2_ ≤ 0.4). In case SBTs are used, an SBT is judged as successful when the following criteria are met for at least 30 min, and the attending physician takes the final decision for extubation:
Respiratory rate < 35 breath/min;Peripheral oxygen saturation > 90%;Increase < 20% of heart rate and blood pressure; andNo signs of anxiety and diaphoresis.

### Data collection

Data will be entered via an electronic case report from (eCRF). On ICU admission and within 48 h, demographic and baseline data and data on disease severity will be collected. Data collection includes gender, age, height, weight, date of hospital admission, date of ICU admission, cause of respiratory failure, chest X-ray, the Sequential Organ Failure Assessment (SOFA) score, the Acute Physiology and Chronic Health Evaluation II (APACHE II) score, and the Simplified Acute Physiology Score II (SAPS II).

Data on the standard of care (described below) will be collected daily for the first 48 h and every 6 h, up to day 28. The total number of hours spent in prone position in a day (cumulative), the number of prone sessions, and their duration is recorded. After the protocol, every day until day 14, clinical outcome variables are discharge of the ICU or death, whichever comes first. Data on duration of noninvasive respiratory support, length of stay in ICU and hospital, location of the patient (in ICU, hospital, another facility, or home), and life status (alive or deceased) will be assessed on 28 and 90 days (Fig. 3).

**Fig. 3 Fig3:**
[figure not shown]
Schedule of events

One hour before each position change (supine to prone and prone to supine), the following variables will be collected for the duration of the protocol: respiratory variables (respiratory rate SpO_2_, SpO_2_/FiO_2_, ROX index; SpO_2_/FiO_2_: RR, dyspnea defined according to the Borg dyspnea scale); noninvasive mean arterial pressure; heart rate; noninvasive support device parameters: Venturi facemask, HFNO, CPAP, NIV; adverse effects possibly related to prone position (hypotension, bradycardia hypoxemia, pressure ulcers, vomiting, displacements of the respiratory support device, peripheral or venous central line, orogastric or nasogastric tube, or urinary catheter), if any are recorded in the eCRF.

In case prone positioning is not tolerated, all reasons for a premature change in body position are reported.

The following parameters of the respiratory support devices will be collected within 1 h before and 1 h after randomization, and every day at a fixed time point until cessation of the respiratory support: Venturi facemask: flow (liters/min), FiO_2_; HFNO: flow (liters/min), FiO_2_; CPAP: PEEP, flow (liters/min), tidal volume, FiO_2_; NIV: PEEP, pressure support over PEEP, flow (liters/min), tidal volume, FiO_2_.

If the patient meets the criteria for intubation, the reasons for intubation are documented in the eCRF.

Data on the administration on the administration of steroids, Remdesivir, Tocilizumab, Heparin/low molecular weight heparin, and antihypertensive medications are recorded. Fluid balance is collected from the nursing chart.

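### Borg dyspnea, oxygenation indices and prone-related adverse effects are timed to prone/supine turns, so matched standard-care records are not assured and poorly tolerated sessions lose their prone reading

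*Protocol article*

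**What the plan says.** All from the protocol article:

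- **Data collection (text below Fig. 3).** The timing rule is "One hour before each position change (supine to prone and prone to supine), the following variables will be collected for the duration of the protocol". The variables include respiratory rate, SpO2, SpO2/FiO2, ROX, "dyspnea defined according to the Borg dyspnea scale", blood pressure, heart rate, and "adverse effects possibly related to prone position (hypotension, bradycardia hypoxemia, pressure ulcers, vomiting, displacements of the respiratory support device" together with line, tube and catheter displacement.
- **Data collection, other schedules.** Respiratory-device settings are taken within an hour either side of randomization and then once a day. Standard-of-care data, said to be described below, are collected daily in the first 48 h and six-hourly up to day 28. Reasons for turning a patient back early are reported, and the number and duration of prone sessions are recorded.
- **Study endpoints.** The list opens with "Secondary endpoints are the effects of awake proning on the following clinical outcome variables". It contains oxygenation parameters, without restriction to one arm, and "Dyspnea sensation (while awake in prone versus supine position").
- **Abstract, Design and methods.** Secondary endpoints include "effects of awake prone positioning on oxygenation parameters, dyspnea sensation, and complications". The comparison is "versus standard care without awake prone positioning".
- **Prone positioning.** Sessions run up to 2 h, with no stated minimum. They may be prolonged for comfort or interrupted for, among other reasons, worsening dyspnea, a sustained SpO2 fall, nausea or vomiting, or hemodynamic instability.
- **Standard of care.** SpO2 and SpO2/FiO2 are monitored continuously in all patients.

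**The concern.** A measurement triggered by the intervention is made only where the intervention is given. If the turn-based rule is the only one that brings Borg scores and the adverse-effect list into the case report form, the standard-care arm has nothing to set against them. What remains is a before/after comparison among treated patients, which is open to recovery and regression to the mean. Hypotension, hypoxemia, vomiting and device displacement also happen to patients who are never proned, so a count in one arm cannot be read as an effect of proning.

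A second problem lies inside the prone arm. The reading meant to describe the patient while prone is set one hour before turning back. Sessions that end early tend to end because of the things being measured, so their missing readings are informative.

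At stake is how the secondary endpoints on dyspnea and oxygenation, and the complications named in the abstract, can be interpreted.

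**Working it through.** The plan gives no figure on this point. The check is a count of trigger points, the timing of the reading, and a comparison of the schedules.

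**1. Trigger points by arm.** There are two turns per block (supine to prone, prone to supine). The Prone positioning section gives four 6-h blocks but also a duration of at least 48 h; 4 × 6 = 24 h, so these two statements need reconciling. Assuming one session per block:

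- 4 blocks: 4 × 2 = 8 turn-triggered records per prone patient.
- 48/6 = 8 blocks: 8 × 2 = 16 records.
- Standard care: 0 turn-triggered records by protocol.

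This counts occasions created by this one rule. It measures neither bias nor everything recorded in controls.

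**2. Do the other schedules fill the gap in controls?**

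| Schedule in the text | Content | Supplies Borg? | Supplies adverse-effect list? | Supplies SpO2/FiO2 and ROX? |
|---|---|---|---|---|
| Device settings around randomization, then daily | Flow, FiO2, PEEP, pressure support, tidal volume | No | No | Not alone: SpO2 and respiratory rate are not listed |
| Standard-of-care data, daily and 6-hourly | Variables not named, timing unclear | Not stated | Not stated | Not stated |
| Continuous monitoring | SpO2, SpO2/FiO2 | No | No | Measured at the bedside; entry in the case report form not stated |

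ROX is SpO2/FiO2 divided by respiratory rate, so FiO2 alone yields neither index.

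**3. When does the prone reading fall?** Take the start of a session as time 0 and its length as T hours. The reading before turning back is at T − 1.

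| T (h) | Reading at (h) | Position at that time |
|---|---|---|
| 2 | 1 | Prone |
| 1.5 | 0.5 | Prone |
| 1 | 0 | Being turned |
| 0.75 | −0.25 | Still supine |
| 0.5 | −0.5 | Still supine |
| 0.25 | −0.75 | Still supine |

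No session with T ≤ 1 gives a reading after any time in prone. For an unplanned stop, T is unknown until it happens, so the reading cannot be scheduled even when T exceeds 1 h.

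The reading before proning is at −1, so the two readings are (T − 1) − (−1) = T hours apart. Better tolerated sessions are therefore also read later.

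**4. Adverse effects.** A record made one hour before a turn precedes anything that happens during that turn, such as displacement of a line or device. The rule also asks for "adverse effects possibly related to prone position". That framing does not prompt for the same event in a patient who was never prone.

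**The case against.** **The schedule of events is not shown.** Fig. 3 is where matched times for both arms would normally stand, and the article condenses a fuller protocol (Version 5.4). This stands. A reader might infer that controls never have these measurements; the text shown cannot establish that.

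**The text has clock-based collection.** The 6-hourly standard-of-care schedule is not limited to one arm, and its reference to a description below may mean this very set of variables. FiO2 is recorded around randomization and daily, and SpO2 is monitored continuously in everyone. This stands against the tempting stronger reading that oxygenation has no randomized comparison. It does not settle Borg or the adverse-effect list, because the schedule names no variables.

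**Dyspnea is defined as prone versus supine.** Measuring it around turns fits that definition, so the lack of an arm comparison is partly by design. This stands. The endpoint is nevertheless introduced as an effect of awake proning, and a within-arm contrast cannot carry that claim.

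**Early-stopped sessions are not unobserved.** The reading before proning, the reason for stopping and the session duration are all recorded, and worsening dyspnea is a stopping criterion at any time. This stands. None of it is stated to supply a Borg or oxygenation value in prone.

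**Adverse effects may be captured as events.** The wording can be read as recording any that occur. The Data and Safety Monitoring Board (DSMB) receives all unexpected adverse events and monitors safety parameters, with no limit by arm (Study organization). A reader might infer that the DSMB has no comparator; that is not supported. But effects listed in advance as possibly related to proning may not count as unexpected, so this route does not assure a matched record of them.

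**Conclusion.** The point holds in a limited form.

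- **Between arms.** On the text shown, matched control records are not assured for Borg dyspnea and the listed adverse effects, and are uncertain for SpO2/FiO2 and ROX.
- **Within the prone arm.** Followed literally, the rule yields no prone reading for any session of 1 h or less and none that can be planned for a session stopped early. The prone-versus-supine contrast leans toward sessions that were tolerated.

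The size of the second effect cannot be given: the documents state no frequency for short or interrupted sessions. The first rests on two assumptions: that Fig. 3 does not already set matched times, and that the standard-of-care schedule does not mean this set. If either assumption fails, what remains is an inconsistency in wording plus the short-session problem.

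Only secondary and safety endpoints are affected. Intubation or death within 14 days does not depend on these records.

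**What to change.** 1. State in Data collection that the whole set, including Borg and the adverse-effect list, is recorded in both arms at the same fixed times from randomization, for example every 6 h to 48 h. Reconcile the standard-of-care schedule and Fig. 3 with this, naming the variables that schedule covers.
2. Add one reading at the actual end of every prone session, including those ended early.
3. Collect the listed adverse effects in both arms regardless of suspected relation to proning, and report them by arm.
4. Label the prone-versus-supine comparison of dyspnea and oxygenation as within-arm and descriptive, and rest any statement about an effect of proning on the between-arm comparison.

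The choice of model can be left to the statistical analysis plan.

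The cost is a change to the electronic case report form and brief 6-hourly recording for 48 h in controls: values largely monitored already, one Borg question and an event check. The prone arm gains an end-of-session entry. Trial status gives recruitment as pending, so the change is best made before the first patient, because readings not taken cannot be recovered later.
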